#### 11.2.4 Follow-up of Adverse Events

- (1) When a medical treatment is necessary to treat an adverse event, the principal investigator or subinvestigator will inform the subject accordingly.
- (2) When an adverse event has occurred, the principal investigator or subinvestigator should discontinue the study drug administration where necessary, secure the safety of the subject by providing appropriate medical treatment, and make an effort to find the cause.
- (3) All subjects experiencing adverse events should be followed until the events resolved. However, a follow-up of an event may be terminated for some medically justifiable reason as described below, and the reason should be specified in the CRF.

Examples:

- When the causal relationship of an adverse event to study drug can be definitely ruled out and it is judged that the safety of the subject can be fully secured.
- When an adverse event is irreversible and the condition of the subject is judged to have become stable.
- When the effect of the study drug appears to have dissolved and further follow-up is not necessary by considering the course and other elements of the adverse event after completion of study drug administration.

### 11.3 Serious Adverse Events

#### 11.3.1 Definition of Serious Adverse Events

A “serious adverse event” among adverse events is defined as follows:

- (1) An event that results in death.
- (2) An event that is life-threatening (i.e. may lead to death).
- (3) An event that results in inpatient hospitalization or prolongation of existing hospitalization.
- (4) An event that results in persistent or significant disability/incapacity.
- (5) An event that results in congenital anomaly.
- (6) Other medically important events that may expose the subject to danger, even though the event is not immediately life-threatening or fatal or does not result in hospitalization, or require medical intervention to prevent such outcome as (1) through (5) above.

#### 11.3.2 Procedures in the Event of a Serious Adverse Event

In the event of a serious adverse event, the procedures as shown below must be followed in addition to those described in “11.2.4 Follow-up of Adverse Events.”

- (1) For all serious adverse events, the principal investigator will inform promptly the head of the study site and the sponsor (monitor) of the event verbally or by telephone or fax or otherwise, followed by a written report using the “Report on Serious Adverse Event Occurring during the Study.” In this report, the principal investigator will determine whether or not the serious adverse event is a serious and unexpected adverse drug reaction (i.e., an adverse drug reaction that was not consistent in nature or severity with the information provided in the Investigator’s Brochure.)
- (2) When additional information on the reported serious adverse event (autopsy report, terminal-stage medical record or other information) is requested by the sponsor, the head of the study site or the IRB, the principal investigator will provide them with such information.
- (3) The sponsor will report every 6 months all serious adverse drug reactions of which causal relationship with the study drug cannot be ruled out to the principal investigator and the head of the study site. Serious adverse events that are unexpected from the information provided in the investigator’s brochure will be immediately reported to the principal investigator and the head of the study site.

## 11.4 Predictable Adverse Drug Reactions

### 11.4.1 Adverse Drug Reactions Predictable from Nonclinical Studies of TS-071

The toxic findings reported in nonclinical studies of TS-071 included soft stools, diarrhoea, watery stools, suppression of body weight gain, decrease in body weight, dark-red focus and erosion in glandular stomach, macroscopic dilatation, dark-red focus, weight increase, mucosal thickening and perforating ulcer in cecum, increased trabecular bone in femur and sternum, decreases in erythrocytes count, hemoglobin and hematocrit, and decrease in the number of corpora lutea. In a one-month repeated-dose oral toxicity study in rats, the death of an animal receiving 500 mg/kg of TS-071 occurred on Day 25 of treatment possibly due to worsening of general condition.

In addition, the adverse events that may occur in association with the pharmacological properties of TS-071 include an increase in urine volume, dehydration, urinary tract infection, an effect on ketones in urine, hypoglycemia, an effect on renal function and an increase in urinary excretion of electrolytes (Ca, P, etc.) due to the promotion of urinary glucose excretion.

### 11.4.2 Adverse Drug Reactions Predictable from Clinical Studies of TS-071

The adverse drug reactions reported in the Phase I single dose study include occult blood positive,  $\beta_2$  microglobulin urine increased, diarrhoea (soft stools) and urethritis. All these adverse drug reactions were mild in severity and reversible. In the Phase I 7-day repeated-dose study, a transient and mild diarrhoea (soft stools) were observed. A transient and mild constipation was reported in the clinical pharmacology study of 7-day repeated administration in patients with type 2 diabetes.

The adverse drug reactions occurring 2 events or more in the Phase II exploratory study include diarrhoea/soft stools, thirst, cystitis,  $\beta$ -N-acetyl-D-glucosaminidase increased, blood urine present, urine ketone body present, headache and pollakiuria. All these adverse drug reactions recovered or were recovering during the treatment period of after the study.

The adverse drug reactions reported in the drug interaction studies include one event of white blood cells urine positive in one subject receiving TS-071 concomitantly with glimepiride, 2 events of nausea in 2 subjects and one event of headache in one subject receiving TS-071 concomitantly with metformin. All these adverse drug reactions were mild in severity and reversible. There were no adverse drug reactions reported after concomitant administration with pioglitazone, voglibose and citagliptin in the drug interaction studies.

The adverse drug reactions reported in the clinical pharmacology study in patients with type 2 diabetes with renal dysfunction were rash and dizziness, both of which were transient and mild in severity.

In the Phase II confirmatory study, adverse drug reactions occurring 2 events or more include constipation, pollakiuria, polyuria/urine output increased, thirst, malaise, pruritus genital, albumin urine present,  $\beta_2$  microglobulin urine increased, urine ketone body present, all of which were mild in severity.

Adverse drug reactions that are predicted to occur include effects on renal function, electrolytes and circulating plasma volume, hypoglycemia and genital and urological infections since TS-071 promotes urinary glucose excretion by inhibiting reabsorption of glucose in the renal tubules.

#### 11.4.3 Measures to be Taken in the Event of Hypoglycemia

In the nonclinical studies [SGLT inhibitory effect in human expressing cells (*in vitro*)], TS-071 demonstrated an inhibitory effect of SGLT and it also inhibited SGLT1, although the effect was not as potent as it inhibited SGLT2: the 50% inhibitory concentration ( $IC_{50}$ ) was 2.26 nmol/L for SGLT2 and 2900 nmol/L for SGLT1. The results of a series of efficacy pharmacology studies suggested that TS-071 exerts its hypoglycemic effect by inhibiting SGLT2 in the proximal renal tubules and promoting urinary glucose excretion. However, the mechanism of suppression of glucose absorption by inhibiting SGLT1 in the small intestines also conceivable. When a hypoglycemic symptom occurred, oral or intravenous glucose should be administered, depending on the symptom, e.g., oral dose for a mild symptom and intravenous dose when the symptom persists, or is severe or emergent.

#### 11.4.4 Adverse Drug Reactions Predictable from Clinical Studies of Avelox® Tablets

The package insert of Avelox® tablets is located in the Attachment.

In the clinical studies of Avelox® tablets in Japan up to the time of approval, adverse drug reactions (including abnormal changes in laboratory tests) were experienced by 130 out of 505 subjects (25.7%). The major events include diarrhoea in 24 subjects (4.8%), liver function test abnormal in 22 subjects (4.4%), nausea in 18 subjects (3.6%), dyspepsia in 14 subjects (2.8%) and abdominal pain in 12 subjects (2.4%). In the foreign clinical studies adverse drug reactions were experienced by 2314 out of 9225 subjects (25.1%). The major events include nausea in 653 subjects (7.1%), diarrhoea in 461 subjects (5.0%) and dizziness in 233 subjects (2.5%).

#### 11.4.5 Measures to be Taken in the Event of Adverse Drug Reaction or Adverse Event Suggestive of TdP

When an adverse drug reaction or adverse event suggestive of TdP occurred, the principal investigator or subinvestigator should discontinue the study drug administration of the subject and the enhancement factors, e.g., hypokalemia and bradycardia, must be corrected. Emergency resuscitation device including a defibrillator will be prepared where necessary. The subject will be sent to a specialized hospital if appropriate measures cannot be taken in the study site. Use of magnesium sulfate by intravenous administration (2 g for 2 to 5 min) should be considered to prevent repeated TdP. Since bradycardia is likely to induce TdP, it should be treated to increase heart rate by a drip infusion of isoproterenol, intravenous administration of atropine sulfate or external pacing.

## 12. Criteria and Procedures for Early Termination of a Subject

### 12.1 Criteria for Early Termination

An early termination is defined as “an occasion when the study is prematurely discontinued by the principal investigator or subinvestigator or because of a subject’s inconvenience or his/her own will before completion of the protocol-directed study procedures.”

The study of a subject will be discontinued according to the procedures provided in “12.2 Procedures for Early Termination” on the occurrence of any of the followings:

- (1) When it is difficult to continue the study because of an adverse event.
- (2) When a QTcF interval of 12-lead ECG for safety assessments increased to  $\geq 500$  msec or increased by  $> 60$  msec from the baseline (prior to study drug administration in each study period), and the principal investigator or subinvestigator finds it difficult to continue the study.
- (3) When a QRS interval of 12-lead ECG for safety assessments increased by  $\geq 25\%$  from the baseline (prior to study drug administration in each study period), and the principal investigator or subinvestigator finds it difficult to continue the study.
- (4) When a significant or continued non-compliance with the protocol that will make it difficult to secure safety or confound the evaluation was identified.
- (5) When a subject is found ineligible in terms of any of the inclusion and exclusion criteria.
- (6) When a subject wishes to withdraw from the study because of an adverse event.
- (7) When a subject wishes to withdraw from the study for a reason other than adverse events.
- (8) When a subject fails to return to the study site and it is difficult to continue the study.
- (9) When the principal investigator or subinvestigator finds it difficult to continue the study for reasons other than those described above.

#### <Rationale>

- (1) This is in consideration of the safety of subjects.
- (2) The QT/QTc Guideline specifies that if there is a marked prolongation of QT/QTc interval to  $> 500$  msec or increase of  $> 60$  msec over the baseline, discontinuation of a subject from a study should be considered.
- (3) “The manual for handling disorders due to adverse drug reactions (MHLW, May, 2009)” states that the dosage should be decreased or drug administration should be discontinued if a QRS interval increased by  $\geq 25\%$  compared to the pre-treatment level.
- (4) This is to eliminate the possibility of compromising the ethical and scientific appropriateness of the study.
- (5) This is intended to ensure early termination of the study for a subject who fails to meet the entry criteria.
- (6) , (7) These are to respect the free will of subjects.
- (8) This will interfere with the protocol-directed evaluation and observation.
- (9) This is to provide against unforeseen contingencies that may require early termination of the study.

## 12.2 Procedures for Early Termination

When a subject meets any of the criteria provided in “12.1 Criteria for Early Termination” during the course of the study, the principal investigator or subinvestigator will perform the study procedures at early termination (see “Appendix 2: Schedule of Study Procedures” and document the results in the CRF. Date of and reason for early termination will also be documented in the CRF.

After discontinuation of the study, appropriate measures should be taken for the subject. When the study was prematurely terminated due to a safety problem, appropriate medical treatments should be provided to the subject and procedures described in “11. Securing the Safety of Subjects” should be followed.

When a subject failed to return to the study site, efforts should be made to ask the subject to return and undergo the study procedures provided in “Appendix 2: Schedule of Study Procedures.”

When it is impossible to perform the study procedure for early termination, the principal investigator or subinvestigator will immediately contact the subject by telephone, correspondence or any other possible means to make a follow-up on the clinical course of the subject after the last observation and any occurrence of an adverse event, and document the results in the CRF. When necessary information on the subject was captured from a person other than the subject for some reason, the reason and the relation of the person to the subject will be documented in the CRF.

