| 12-lead ECG for QT/QTc analysis* | Pre-dose and 0.5, 1, 2, 3, 4, 6, 8, 24 hr post-dose in each study period |

\*: 12-lead ECG will be recorded in the supine position after resting for 10 min.

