##### 13.3.2.3 Handling of Missing Values

When a data is missing or excluded from analysis, continuous value of such data will be excluded from summary/analysis, and discrete value of such data will be handled as unknown.

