| Hospitalization (4 days & 3 nights)          |                 |                  |                       | ←                |                                           |   |     |   |   |   |       |   |   |        |       |           |       |                 |                               |                   |     |   |   |
| Study drug administration                    |                 |                  |                       |                  |                                           | X |     |   |   |   |       |   |   |        |       |           |       |                 |                               |                   |     |   |   |
| Meal *1                                      |                 |                  |                       | Supper *2        |                                           |   |     |   |   |   | Lunch |   |   | Supper |       | Breakfast | Lunch | Supper          | Breakfast                     |                   |     |   |   |
| Physical examination                         |                 |                  | X                     | ←                |                                           |   |     |   |   |   |       |   |   |        |       |           |       |                 |                               |                   | X   | X |   |
| Height, weight                               |                 |                  | X                     |                  |                                           |   |     |   |   |   |       |   |   |        |       |           |       |                 |                               |                   |     |   |   |
| Body temperature, blood pressure, pulse rate |                 |                  | X                     |                  | X                                         |   | X   | X | X | X | X     |   |   |        |       | X         |       |                 | X                             | X                 | X   |   |   |
| 12-lead ECG for QT/QTc analysis              |                 |                  |                       |                  | X                                         |   | X   | X | X | X | X     | X |   |        |       | X         |       |                 |                               |                   |     |   |   |

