| 12-lead ECG for safety analysis              |                 |                  | X *3                  |                  | X *3                                      |   | X   | X | X | X | X     | X |   |        | X     | X         |       |                 | X                             | X                 | X   |   |   |
| Blood collection for pharmacokinetics *4     |                 |                  |                       |                  | X                                         |   | X   | X | X | X | X     | X |   |        | X     | X         |       |                 | X                             |                   | X*6 |   |   |
| Clinical laboratory tests *4                 | Hematology      |                  | X                     | (X)              | X                                         |   |     |   |   |   |       |   |   |        |       | X         |       |                 |                               | X                 | X   |   |   |
|                                              | Blood chemistry |                  | X                     | (X)              | X                                         |   |     |   |   |   |       |   |   |        |       | X         |       |                 |                               | X                 | X   |   |   |
|                                              | Urinalysis      |                  | X                     | (X)              | X                                         |   |     |   |   |   |       |   |   |        |       | X         |       |                 |                               | X                 | X   |   |   |
| Immunology tests                             |                 |                  | X                     |                  |                                           |   |     |   |   |   |       |   |   |        |       |           |       |                 |                               |                   |     |   |   |
| Urine drug screen                            |                 |                  | X                     |                  |                                           |   |     |   |   |   |       |   |   |        |       |           |       |                 |                               |                   |     |   |   |

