| Pregnancy status (female only)               |                 |                  | X                     |                  | X                                         |   |     |   |   |   |       |   |   |        |       |           |       |                 |                               | X                 | X   |   |   |
| Adverse event monitoring                     |                 |                  |                       |                  |                                           | ← |     |   |   |   |       |   |   |        |       |           |       |                 |                               |                   |     | X | X |

The schedule from Day -1 to Day 3 will be consistent for each period. The examination/observation displayed as "(X)" will be conducted in Period 1 only.

\*1: If meal time coincides with examination or blood collection, meal will be provided after the examination or blood collection.

Contents of meals during hospitalization (from supper on Day -1 through breakfast at 48 hr post-dose) will be consistent for the same subject from Period 1 through Period 4.

\*2: The supper will be provided ≥ 10 hours prior to study drug administration.

\*3: Exclusion criteria (5) and (6) will be checked at screening and prior to study drug administration in Period 1.

\*4: If blood collection coincides with 12-lead ECG recording, blood will be collected after 12-lead ECG.

\*5: Post-treatment examination will be conducted with an interval of ≥ 7 days after the final study drug administration (on Day 8 or thereafter when Day 1 is the day of study drug administration in Period 4).

\*6: These will be conducted only when the study was terminated between study drug administration and 48 hours post-dose in each period.

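### Early termination does not separate ending dosing from ending measurement, so a subject discontinued after a dose may be missing from later time points of the QTcF analysis

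*Protocol*

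**What the plan says.** Protocol 12.1 describes early termination as stopping the study for a subject before the planned procedures are complete, and introduces its nine criteria with "The study of a subject will be discontinued according to the procedures provided in" section 12.2. What ends is the subject's participation, not only further dosing. Criterion (2) uses the primary variable: QTcF on the safety ECG of 500 msec or more, or a rise of more than 60 msec over the period's baseline, "and the principal investigator or subinvestigator finds it difficult to continue the study". Criterion (3) has the same structure for QRS.

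Section 12.2 then says "the principal investigator or subinvestigator will perform the study procedures at early termination" and points to Appendix 2. In that table's early-termination column:

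- the row "12-lead ECG for safety analysis" is marked;
- PK blood sampling is marked with footnote *6: "These will be conducted only when the study was terminated between study drug administration and 48 hours post-dose in each period";
- the row "12-lead ECG for QT/QTc analysis" shows no mark.

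Table 10-2 in 10.8 sets the centrally read recordings at "Pre-dose and 0.5, 1, 2, 3, 4, 6, 8, 24 hr post-dose in each study period" and has no early-termination time point. Section 13.3.2.3 adds: "When a data is missing or excluded from analysis, continuous value of such data will be excluded from summary/analysis". Under 13.4.3.1, TS-071 is called negative only if the upper one-sided 95% bound excludes 10 msec at all time points.

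**The concern.** Within a period, the single dose has already been given when a post-dose criterion is met, so ending participation ends measurement and nothing else in that period. If one reason for ending it is a long QTcF, the missing values depend on the outcome being estimated. Dropping them lowers the later TS-071 means and their upper bounds, which favours a negative conclusion. Mean Tmax in 9.1.3 is 1.06 to 2.25 hr for TS-071, so a subject discontinued at 1 or 2 hr could miss time points close to peak exposure.

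Footnote *6 shows that termination within a period was foreseen. A concentration is kept for it, but no paired central ECG, although 13.4.3.1 plans plots of ΔΔQTcF against concentration. Recordings that were never made cannot be recovered by a later analysis plan.

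**Working it through.** **1. The plan's own figure.** The document gives 56 subjects (9.3), which is 4 sequences of 14. It gives no SD, assumed effect, power or dropout rate, so 56 cannot be reproduced and is taken as given.

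**2. Inputs.** From the Protocol: n = 56, margin 10 msec, one-sided 95% bound. Assumed, because the Protocol gives no values: mean ΔΔQTcF in the remaining subjects m = 3 to 7 msec; SD of the paired difference 8 to 14 msec; residual effect in a lost responder E = 30 to 60 msec; number lost k = 1 to 3. Simple paired means stand in for the covariance-adjusted means.

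**3. Shift in a later mean.** With all subjects kept, the mean is [(56 − k)m + kE]/56. Without the k responders it is m. The shift is therefore k(E − m)/56.

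- k = 1, E = 30: (30 − 7)/56 = 0.41 to (30 − 3)/56 = 0.48 msec
- k = 1, E = 60: (60 − 7)/56 = 0.95 to (60 − 3)/56 = 1.02 msec
- k = 2, E = 60: 1.89 to 2.04 msec
- k = 3, E = 60: 2.84 to 3.05 msec

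**4. Is 30 to 60 msec plausible at later times?** As an illustration, suppose +60 msec at 2 hr, proportional to concentration and falling with a 13 hr half-life (9.1.3 gives 12.6 and 13.8 hr for 25 and 15 mg). Then 60 × 0.5^((t − 2)/13) is 53.9 at 4 hr, 48.5 at 6 hr, 43.6 at 8 hr and 18.6 at 24 hr. The range suits 4 to 8 hr. At 24 hr the shift is smaller: (18.6 − 5)/56 = 0.24 msec with m = 5.

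**5. Effect on the upper bound.** Bound = mean + t(0.95) × SD/√n. When responders are kept, the SD is recomputed with them included. Results for E = 60:

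| m | SD | k | bound, kept | bound, lost | conclusion changes |
|---|---|---|---|---|---|
| 3 | 10 | 3 | 9.67 | 5.30 | no |
| 3 | 14 | 3 | 10.25 | 6.22 | yes |
| 5 | 10 | 1 | 8.74 | 7.26 | no |
| 5 | 10 | 2 | 10.15 | 7.28 | yes |
| 7 | 8 | 1 | 10.32 | 8.81 | yes |
| 7 | 10 | 1 | 10.67 | 9.26 | yes |
| 7 | 14 | 1 | 11.43 | 10.16 | no, above 10 either way |

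Among the values tried (m = 3, 5, 7; SD = 8, 10, 14), losing a single subject changed the conclusion only at m = 7 with SD 8 or 10 and E = 60, where the bound without that subject was already 8.8 to 9.3 msec.

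**The case against.** Several points on the other side stand.

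- **Timing.** A reader might infer that recording stops at once. Section 12.2 gives no timing and does not cancel the period's remaining recordings; it simply does not provide for them.
- **Discretion.** A reader might infer that the strongest responders must go missing. Criteria (2) and (3) also require the investigator to find continuation difficult, so an investigator could complete the period and then end participation. The text supports only that they may go missing.
- **Readings already taken.** A triplicate recorded at the triggering time stays in the mean for that time point and in the categorical counts of 13.4.3.1.
- **Duration of prolongation.** It would be wrong to say this information is lost. Under 10.10, a change judged abnormal is followed as an adverse event, normally until recovery, and 10.9 evaluates all ECGs for safety. What may be lost is the centrally read series; 10.8 sends only the QT/QTc-analysis charts to the central facility.
- **Appendix 2.** The copy of the table read here is partly damaged. Its QT/QTc and PK rows lack an 8 hr mark that Tables 10-2 and 10-4 require, so a missing early-termination mark is weak evidence alone. Table 10-2 supports it independently by listing no such time point.
- **Other documents.** The separate ECG procedure and the criteria for handling cases and data are not shown and may add detail. They would not remove the gap in 12.2.

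With the other subjects near 0 msec and an SD of 10, the bound is about 2.3 msec with one responder lost, 3.9 with one kept and 5.5 with two kept. All are well below 10.

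**Conclusion.** The gap is real and modest. Sections 12.1 and 12.2 do not separate stopping further dosing from stopping measurement, and no section provides for the remaining central QT/QTc ECGs of a period whose dose has been given. Any resulting loss can depend on the outcome, and in the TS-071 periods it favours a negative finding.

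The size is about 0.4 to 1.0 msec per lost subject at a time point, assuming n = 56, residual effects of 30 to 60 msec and a mean of 3 to 7 msec in the others. The paired calculation also takes the subject's placebo period as available; if it still lay ahead, the size would depend on the analysis model. A reader might infer that the trial's conclusion is unsafe. The calculation does not support that: the conclusion changes only when the bound is already near 10 msec or several responders are lost, and such subjects should be rare among healthy volunteers. In the Avelox period the same loss lowers the estimate, which is conservative for assay sensitivity.

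The change is worth making because it is cheap and analysis cannot replace unrecorded ECGs.

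**What to change.** Change data collection only; the stopping criteria and clinical management stay as they are.

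- In 12.2 and Appendix 2, state that after discontinuation following a dose, with the subject's agreement and where the investigator judges it medically feasible, the remaining scheduled QT/QTc-analysis ECGs (to 24 hr) and PK samples (to 48 hr) of the current period are still taken. The ECGs are read centrally and the data are included in the analysis.
- In the early-termination column of Appendix 2, add the QT/QTc-analysis ECG under the same *6 condition as PK, and bring Table 10-2 into line.

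The cost is a short amendment, plus a few 10-second recordings and blood samples in a rare discontinued subject who would otherwise have had them. The planned hospital stay already covers 48 hr after the dose.
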